## Background

Pressure ulcers are a leading cause of morbidity (and in some instances, mortality) in hospitalized and institutionalized patients (Woodbury), resulting in substantial financial costs to hospitals and personal costs borne by affected patients and their families. A pressure ulcer is "a localized injury to the skin and/or underlying tissue over a bony prominence, as a result of pressure, or pressure in combination with shear (NPUAP)." The size and severity of pressure ulcers vary, ranging from skin erythema to full thickness tissue loss with damage extending into muscle and bone (NPUAP Staging). Annually, there are

Ethics ID number: REB13-0794

Study Title: Effectiveness of a pressure-sensing mattress system for reducing the risk of pressure ulcer formation by lowering interface pressure in vulnerable patient populations: Parallel-two-group randomized trial

PI: [name]

Version number/date: V2 01/04/2014

an estimated 250,000 to 500,000 individuals affected by pressure ulceration in Canada, with the overall estimated prevalence in all health-care institutions to be 26.0% in Canada (Dealey, Wound Care in Canada).

Pressure ulcer development and recurrence is multi-factorial; however, they primarily occur in people who have limited mobility, nerve damage, or both. Risk factors include limited mobility and activity; perfusion (including diabetes); skin conditions; skin moisture and incontinence; advanced age; reduced levels of albumin, haemoglobin/anaemia, lymphocytes, and other blood serum components; compromised nutritional status; and general health status (Coleman, Dorner). Other predictors of pressure ulceration include ICU admission length, norepinephrine administration, and cardiovascular disease among adult critical care patients (Cox), while delayed and inappropriate medical management, history of or existing pressure ulceration, and limited independence in self-care were also predictors among adults with spinal cord injuries (Marin).

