## **Objectives**

The primary objective of this study is to:

1. establish the effectiveness of a pressure-sensing mattress system (ForeSite PT™ system) in its ability to reduce interface pressure as reflected in a composite of pressure measurements.

Ethics ID number: REB13-0794

Study Title: Effectiveness of a pressure-sensing mattress system for reducing the risk of pressure ulcer formation by lowering interface pressure in vulnerable patient populations: Parallel-two-group randomized trial

PI: [name]

Version number/date: V2 01/04/2014

The secondary objectives are to:

1. assess whether the ForeSite PT™ system reduces the incidence of pressure-related compromised skin and soft tissues, with potential for progression to overt pressure ulceration;
2. determine the minimum interface pressure that is associated with higher risk for pressure ulcer development through the correlation of clinical outcomes and pressure outcomes;
3. assess healthcare provider and patient perceptions of the ForeSite PT™ system; and
4. establish the cost-effectiveness of the ForeSite PT™ system.

Specifically, the study will address the following research questions:

1. Is the ForeSite PT™ system effective at reducing interface pressure by assisting healthcare providers in determining the best method for patient turning/repositioning?
2. Does the use of the ForeSite PT™ system reduce the incidence of pressure-related compromised skin and soft tissues, with potential for progression to overt pressure ulceration?
3. Does interface pressure correlate with clinical outcomes?
4. Does the ForeSite PT™ system have more impact on the clinical outcomes of patients who have been identified as having a higher risk of pressure ulceration as per the Braden scale?
5. What are the perceptions (both positive and negative) of healthcare providers to the ForeSite PT™ system with regards to functionality, ease of use, and interpretation of pressure data on the computer monitor?
6. What are the perceptions (both positive and negative) of patients (and if appropriate, family members) to the ForeSite PT™ system (including sensor pad and monitor display of their pressure points)?

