### 205 **Secondary Outcomes**

Ethics ID number: REB13-0794

Study Title: Effectiveness of a pressure-sensing mattress system for reducing the risk of pressure ulcer formation  
by lowering interface pressure in vulnerable patient populations: Parallel-two-group randomized trial

PI: [name]

Version number/date: V2 01/04/2014

- 206 1. A composite of endpoints that reflect compromised skin and soft tissues, with potential for  
 207 progression to overt pressure ulceration. This will include:  
 208 a. skin discolouration;  
 209 b. localized tenderness without skin breakdown;  
 210 c. Stage I and II (partial thickness) pressure ulcer formation;  
 211 d. Stage III and IV (full thickness) pressure ulcer formation;  
 212 e. unstageable/Unclassified: Full thickness skin or tissue loss – depth unknown;  
 213 f. suspected Deep Tissue Injury – depth unknown; or  
 214 g. presence of any skin or wound infection (i.e., cellulitis, infected ulcers, or osteomyelitis).

215 This outcome will be measured by a head-to-toe skin clinical assessment for detection of pressure-  
 216 related skin changes and for overt ulceration by the Research Nurse. This assessment will be conducted  
 217 within 24 hours of admission and 24 hours prior to discharge, or on the seventh day (whichever comes  
 218 first). This information will be noted on a form, which requires the Research Nurse to circle the skin  
 219 areas where the patient may have skin changes or a pressure ulcer. They will label the circled area with  
 220 the numbers 1 to 9 that correspond to predetermined categories of pressure-related skin changes and  
 221 stages of pressure ulcer development.

222 The presence of a pressure ulcer and its severity, as well as the development of other skin condition  
 223 changes, will be determined as per the National Pressure Ulcer Advisory Panel's categories/staging  
 224 definitions (2,3,4,5,6,7) and other skin appearance changes (1,8,9) described below:

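### The skin composite has no rule for lesions already present at entry, so carried-in lesions may count against an incidence objective; some of its items also have no code on the form

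*Protocol*

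**What the plan says.** All references are to the Protocol.

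- **Objective.** Objectives, secondary objective 1, is to establish whether the system "reduces the incidence of pressure-related compromised skin and soft tissues, with potential for progression to overt pressure ulceration". Research question 2 repeats the word incidence.
- **Eligibility.** None of the inclusion or exclusion criteria concerns existing ulcers or skin change.
- **Composite.** Under Secondary Outcomes, item 1, components c and d are worded as events (for example "Stage I and II (partial thickness) pressure ulcer formation"). Components a, b, e and f are bare states, including "localized tenderness without skin breakdown". Component g is the "presence of any skin or wound infection (i.e., cellulitis, infected ulcers, or osteomyelitis". The sentence that brings in the staging definitions reads "The presence of a pressure ulcer and its severity, as well as the development of other skin condition" and goes on to say that these are classified by the cited staging system.
- **Timing.** The head-to-toe examination is made "within 24 hours of admission and 24 hours prior to discharge, or on the seventh day (whichever comes" first). Lesions are circled by body area and labelled 1 to 9 both times. The purpose given for the baseline assessments is to describe the patient at entry.
- **Analysis.** Analysis and Statistical Methods gives chi-square or Fisher tests between groups, with logistic regression only if important baseline characteristics differ notably. Patients are stratified by Braden score, and none of its six subscales records existing lesions.

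**The concern.** An incidence objective needs a rule that separates lesions arising during the trial from lesions brought into it. The Protocol has both body maps but never says how they combine into one patient's event status. A patient admitted with an ulcer that is still there on day 7 could count as an event, be excluded, or count only if a new or worse lesion appears. The wording gives some support to each reading.

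The analysis section does not close the gap. Randomization tends to balance carried-in lesions between arms, and balance is the situation in which the planned adjustment is not triggered. Balanced carried-in lesions add about the same number of events to both arms. That leaves no bias in the test of no effect, but it shrinks the contrast and costs power. Lesions that predate monitoring would also blur the planned correlation of interface pressure with skin outcomes.

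A second matter concerns the instrument. The composite is measured on a form with nine labels, and the labels do not cover everything the composite lists. What is not coded at the bedside cannot be derived later.

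**Working it through.** **1. Inputs.** Event rates of 30% and 20%, alpha 0.05, 80% power, 294 needed and 300 randomized per arm come from Sample size, where they are stated for the primary outcome. The Protocol gives no rate for the skin composite, so using 30% and 20% as new-lesion risks is an assumption. The only prevalence figure is in Background: "overall estimated prevalence in all health-care institutions to be 26.0% in Canada". It covers ulcers in all institutions, not this composite in the trial units, so 10% is shown beside it.

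**2. Reproducing the stated figure.** Two-sided test, pooled variance, no continuity correction:

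n = [1.960·√(2·0.25·0.75) + 0.842·√(0.30·0.70 + 0.20·0.80)]² / 0.10² = [1.200 + 0.512]² / 0.01 ≈ 293.2, so 294 per arm. This matches. Power at 300 per arm is 80.9%. No sample-size figure is wrong on this point.

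**3. If presence at the last examination were the score.** Let b be the share with a lesion at entry, r the share of those whose lesion persists, and q the new-lesion risk. Then

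p = b·[r + (1 − r)·q] + (1 − b)·q, which for r = 1 is b + (1 − b)·q.

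- b = 10%, r = 1: 0.10 + 0.90·0.30 = 37.0%; 0.10 + 0.90·0.20 = 28.0%.
- b = 26%, r = 1: 0.26 + 0.74·0.30 = 48.2%; 0.26 + 0.74·0.20 = 40.8%.
- b = 26%, r = 0.5: 0.26·0.65 + 0.222 = 39.1%; 0.26·0.60 + 0.148 = 30.4%.

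Power = Φ{[|p₁ − p₂|·√n − 1.960·√(2p̄(1 − p̄))] / √(p₁(1 − p₁) + p₂(1 − p₂))} with n = 300. For b = 26%, r = 1: [0.074·17.32 − 1.960·0.7028] / 0.7009 = −0.137, so 44.6%.

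**4. If only new lesions count.** If every patient can have one, the comparison is 30% vs 20% with 300 per arm. If it is limited to patients free of lesions at entry, n falls to 300·(1 − b): 270 at b = 10%, 222 at b = 26%.

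| Scoring | Rates | Relative reduction | Power |
|---|---|---|---|
| Presence, b = 10%, all persist | 37.0% vs 28.0% | 24% | 65.4% |
| Presence, b = 26%, all persist | 48.2% vs 40.8% | 15% | 44.6% |
| Presence, b = 26%, half persist | 39.1% vs 30.4% | 22% | 61.0% |
| New lesions, all 300 per arm at risk | 30% vs 20% | 33% | 80.9% |
| New lesions, lesion-free only, b = 10% | 30% vs 20% | 33% | 76.7% |
| New lesions, lesion-free only, b = 26% | 30% vs 20% | 33% | 68.3% |

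**5. Components against form labels.** Components c to f map to labels 2 to 7, and infected ulcers in component g map to label 9. Three items have no code:

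- Tenderness without breakdown (component b): no label. Label 2 mentions pain only as a possible feature of a Stage I ulcer.
- Osteomyelitis (component g): no label. The description of label 5 mentions it only as a likely complication.
- Cellulitis away from an ulcer: component g covers any skin infection, label 8 covers only cellulitis around an ulcer, and label 1 excludes cellulitis.

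**The case against.** A reader might infer that the Protocol scores the composite as presence at the final examination and so measures prevalence. It does not say this. The sentence that speaks of presence states which staging definitions apply, not which visit is scored. The objective says incidence, components c and d imply new events, and the outcome is said to be measured by examinations at both times. A chi-square test works as well on a new-lesion indicator as on a presence indicator. This part of the objection stands: the fault is an undefined and inconsistently worded event, not a declared prevalence endpoint.

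A reader might also infer a wrong count of events averted in the economic evaluation. On the model above, presence scoring gives 300 × 0.074 = 22.2 fewer events per arm, and new lesions among the lesion-free give 222 × 0.10 = 22.2. The counts agree. They would part only if patients with a carried-in lesion also gained new lesions that presence scoring hid. The economic section moreover refers to pressure ulcers, not to this composite. That claim is not supported.

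The power figures stack assumptions: rates from another outcome, a national prevalence, and persistence, although label 1 describes a potentially reversible change. They also assume that the system does not alter lesions already present, while Background presents the technology for management as well as prevention. This too stands, and the figures are illustrations only.

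Finally, a statistical analysis plan, not seen here, could hold the derivation rule. That weakens the point but does not remove it: the mixed wording sits in the Protocol's own endpoint definition, its adjustment rule leaves balanced carried-in lesions unhandled, and no analysis plan can recover findings that the form does not code.

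**Conclusion.** The point holds as one of definition. The objective is incidence, patients with lesions are eligible, the composite mixes three event concepts, and nothing links the two skin maps. The plan therefore permits carried-in lesions to count and dilute the effect. Whether that happens depends on a rule the Protocol does not give. If it did, the loss could be material: about 65% power at 10% baseline prevalence and 45% at 26% with full persistence (61% with half), against about 81% when only new lesions count and all patients are at risk. All of this rests on borrowed 30% and 20% risks; the Protocol claims no power for this outcome.

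The mismatch between components b and g and labels 1 to 9 rests on no assumption. Those items cannot be derived from the form as written; the other components are not affected by this gap. For a secondary outcome, both matters should be corrected, but neither undermines the primary comparison.

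**What to change.** 1. Define the event per patient as at least one new or worsened lesion by body site against the baseline map: a label not present at that site at entry, or a higher stage there. Use the same term throughout the objective, the component list and the staging sentence.
2. Keep patients with baseline lesions in the analysis and adjust the between-group comparison for baseline lesion status in all cases, not only after observed imbalance. The logistic regression already named would serve. Limiting the analysis to lesion-free patients is cleaner in concept but gives up sample size, as the table shows.
3. Align components a to g with labels 1 to 9: add codes for tenderness alone, osteomyelitis and cellulitis away from an ulcer, or delete those items from the composite.

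Both maps are already collected, so the cost is revised wording, slightly more derivation work and a small form edit. The form edit has to precede data collection to be of use.

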### **Sample size**

A total of 600 patients will be recruited from Unit 36, Unit 58, and the ICU will be enrolled in the trial, in order to randomize 300 patients to each of the intervention and control arms. Sample size estimates for the primary outcome indicate a need for 294 patients in each of the intervention and control arms. This is based on an estimated control group event rate of 30%, an intervention group rate of 20% (i.e., a 33% relative risk reduction), an alpha level of 0.05, and 80% power.

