## 190 **Outcomes**

### 191 **Primary Outcome**

- 192 1. A composite of interface pressure measurements that reflect the distribution of interface pressure  
193 at predetermined time intervals. These measures include:
- 194 a. proportion of participants that have pressure readings greater than 40 mmHg;
  - 195 b. average interface pressure (excluding sensels with 0mmHg reading); and
  - 196 c. the absolute number of sensels with pressure readings greater than 40 mmHg.

197 The measurement of this outcome will be facilitated by the ForeSite PT™ system's sensor overlay that  
198 continuously collects pressure readings. The array of the sensor overlay is a capacitive sensor with a  
199 0.625" spatial resolution. There are 52 rows x 118 columns for 6,136 sensing points. The ForeSite PT™  
200 system's software continuously samples interface pressure at a rate of 1 Hz, which can then be  
201 extracted for analysis. The data file is in a proprietary binary format, and can be exported to TXT or CSV  
202 formats for import into a spreadsheet program for analysis. This will be achieved by the sampling of  
203 pressure readings at specified time intervals before and after turning/repositioning when the ForeSite  
204 PT™ system's LCD monitor is turned on, and when it is turned off.

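### The 294 per arm and 80% power claimed for the primary outcome rest on an unnamed 30% vs 20% event that can match at most one of its three components

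*Protocol*

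**What the plan says.** The Sample size section of the Protocol states: "Sample size estimates for the primary outcome indicate a need for 294 patients in each of the intervention and control arms". It continues: "This is based on an estimated control group event rate of 30%, an intervention group rate of 20" percent, described as a 33% relative risk reduction, with "an alpha level of 0.05, and 80% power". Recruitment is set at 600, "in order to randomize 300 patients to each of the intervention and control arms". The section does not say what the event is.

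The Primary Outcome section defines a composite of interface pressure measures taken at predetermined intervals:

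- (a) "proportion of participants that have pressure readings greater than 40 mmHg";
- (b) mean interface pressure, leaving out sensels that read zero;
- (c) the number of sensels reading above 40 mmHg.

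On the device it says: "There are 52 rows x 118 columns for 6,136 sensing points". Sampling is continuous at 1 Hz. The readings for analysis are drawn at specified times before and after repositioning.

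Analysis and Statistical Methods plans Chi-square and/or Fisher exact tests for the primary and secondary outcomes. The same section calls the primary endpoint pressure distribution.

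**The concern.** A two-proportion calculation powers one yes/no result per participant. The primary outcome as defined is one binary measure, one continuous measure and one count, and the Protocol does not say how they become a single result. The 80% figure therefore cannot describe the primary outcome as a whole, although the Sample size section presents it that way.

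The justification for 600 participants is at stake. A reader cannot tell what difference in mean pressure or in sensel count the trial can detect. Nor can a reader tell whether success means a result on (a), on any one component, or on all three. The tests named for the primary outcome suit proportions; applied to (b) or (c) they would need a cut-point that the Protocol does not give.

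A further question concerns (a). As worded it sets no minimum number of sensels and no minimum duration. With 6,136 sensing points under each participant, nearly everyone might have some reading above 40 mmHg, and (a) would then separate the arms poorly.

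**Working it through.** **Inputs (Protocol, Sample size):** p1 = 0.30, p2 = 0.20, alpha 0.05, power 0.80, 1:1 allocation, 300 per arm planned. Sidedness is not stated; two-sided is assumed because it reproduces the figure.

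**1. Reproduce 294.** Pooled-variance formula, no continuity correction, mean rate 0.25:

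n = [1.960 × √(2 × 0.25 × 0.75) + 0.842 × √(0.30 × 0.70 + 0.20 × 0.80)]² / (0.10)²

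= [1.960 × 0.6124 + 0.842 × 0.6083]² / 0.01 = (1.2002 + 0.5119)² / 0.01 = 293.2, rounded up to 294.

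This matches exactly. A one-sided test would give 231, and a continuity correction 313.

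**2. Power at 300 per arm.** z = (0.10 × √300 − 1.2002) / 0.6083 = (1.7321 − 1.2002) / 0.6083 = 0.874, so power is 80.9%.

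**3. Match the calculation to the endpoint.**

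| Component | Type | Can it have a 30% vs 20% event rate? | Inputs given for power | Does Chi-square/Fisher fit? |
|---|---|---|---|---|
| (a) participants with readings above 40 mmHg | binary | yes, if (a) is the event | 30% and 20%, no source | yes |
| (b) mean pressure | continuous | no | none | no |
| (c) number of sensels above 40 mmHg | count | no | none | no |
| composite of the three | undefined | no combining rule | none | cannot be judged |

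**4. What (a) as the event would imply.** If (a) and (c) use the same sampled readings, a 30% vs 20% rate on (a) means that (c) is zero in 100% − 30% = 70% of controls and 100% − 20% = 80% of the intervention arm. The Protocol does not say whether this is expected.

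**5. What 300 per arm supports for a continuous measure.** Detectable standardised difference at 80% power, normal approximation:

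- two-sided 0.05: (1.960 + 0.842) × √(2/300) = 2.802 × 0.0816 = 0.229 SD;
- each of three components at 0.05/3: (2.394 + 0.842) × 0.0816 = 0.264 SD.

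The Protocol gives no SD or target difference, so these cannot be turned into mmHg or numbers of sensels.

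**6. If (a) were one of three components, each tested at 0.05/3 (an assumption).** 30% vs 20% would need (2.394 × 0.6124 + 0.5119)² / 0.01 = 391.2, so 392 per arm. With 300 per arm, power is 66.9%.

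**7. How far power for (a) depends on the unsourced 30% (assumed rates).** For a 10-point absolute drop at 300 per arm, power is 93% from 20%, 81% from 30%, 69% from 50%, 73% from 70% and 93% from 90%. Near the ceiling only smaller drops may be available: 95% vs 90% has 64% power, and 99% vs 97% has 42%. These rates are illustrations; the Protocol gives no distribution of readings around 40 mmHg.

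**The case against.** The best defence is that the Sample size section says the figure is for the primary outcome, that (a) is a proportion of participants, and that the planned tests are tests of proportions. These three facts fit a reading in which (a) is the event. This stands, and on that reading 294 per arm and about 81% power at 300 are correct for (a). It does not rescue the claim for (b), (c) or the composite.

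Two stronger readings are tempting, and the Protocol supports neither.

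- A reader might infer that 30% and 20% are really rates for the secondary skin and soft-tissue composite, so that the event is not the primary outcome at all. No passage links the rates to that composite, and the reading above remains open.
- A reader might infer that (a) is close to 100% in both arms because of the number of sensors and the 1 Hz sampling over up to 7 days. The Protocol takes readings at predetermined intervals and around repositioning, not over the whole stream, and says nothing about how often 40 mmHg is exceeded. Saturation is plausible, but it is not shown.

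It can also be said that 0.23 SD is worked back from 600 patients and so justifies nothing by itself. That is fair: it states what the trial can detect, and the sponsor must say whether such a difference matters.

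A statistical analysis plan, not seen here, may define the endpoint more closely. The mismatch would remain, because the Protocol itself makes the power claim and defines the outcome.

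**Conclusion.** The point holds as an endpoint mismatch, not as an error of arithmetic. The 294 reproduces exactly, and 300 per arm gives 80.9% power for 30% vs 20% (two-sided 0.05, no continuity correction). The event is unnamed and can be component (a) at most. The Protocol gives no power for mean pressure, the sensel count or the composite, and names tests that do not suit the first two.

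No corrected sample size can be derived, since there is no SD, no target difference and no combining rule. What can be said is that 300 per arm detects about 0.23 SD in a single continuous measure, or about 0.26 SD if three components share alpha equally. Both figures assume approximate normality and no losses. Whether (a) sits near its ceiling remains an open question for the sponsor.

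**What to change.** No change in the number of patients is needed.

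1. Name one primary pressure measure, or state a rule that turns the three components into one result per participant, and name a test that fits it.
2. Restate the power claim for that measure. If it is continuous, say that 300 per arm has 80% power for about 0.23 SD (about 0.26 SD if three components are each tested at 0.05/3), and say why that difference matters. If it is (a), say that 30% and 20% refer to (a) only and give the basis for 30%.
3. Preferably express (a) per patient, as the share of sampled time or of loaded sensels above 40 mmHg, so that it cannot saturate. It then becomes a continuous measure and falls under the continuous case in step 2.
4. Label the 30% vs 20% calculation as belonging to the skin composite only if the sponsor confirms that source.

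The cost is rewording in the Sample size, Primary Outcome and analysis sections. Steps 1 and 3 alter how the primary outcome is defined, so they should be settled before any comparison by arm is seen. The stated power becomes narrower or less favourable. No extra data are required, because the sensor overlay already records the readings.
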